### Randomization

The allocation of the participants to the different groups will occur using a simple lottery procedure. Treatment codes (active or sham stimulation) will be placed in opaque envelopes [47, 48]. A researcher not involved in the evaluations or treatment will be responsible for the random allocation of the participants to two groups: 1) active tDCS combined with physical therapy for the upper limbs using a “mini-bike”; or 2) sham tDCS combined with physical therapy for the upper limbs using a “mini-bike”.

### Blinding

The NeuroConn DC-STIMULATOR PLUS device has settings that enable the selection of the active stimulation mode or sham mode by entering codes. A researcher not involved in the treatment or evaluations will program the equipment with the code to which the patient was allocated. The type of stimulation (active or sham) will not be perceptible by visual cues or the external functioning of the device. Therefore, neither the researcher who will place the equipment on the patient nor the patient will know which treatment he/she is receiving (a double-blind study).

### Data collection, management, and analysis

All evaluations will be performed prior at baseline (preintervention), after the 10 treatment sessions (postintervention), and 30 days after the end of the treatment sessions (follow-up).

### Pain intensity

Pain intensity will be measured using the VAS, which consists of a horizontal straight line measuring 10 cm, with 0 cm corresponding to the absence of pain and 10 cm corresponding to maximum pain [46, 49]. The interobserver and intraobserver reliability of this measure have been demonstrated using the intraclass correlation coefficient (ICC; 0.96 to 0.98) [49]. The assessments will be performed with the patient at rest (lying down) as well as during the active (performed by the subject) and passive movements (performed by the researcher) of the painful upper limb on three occasions: preintervention, postintervention, and 30-day follow-up. The intensity of the pain to be considered will be the pain at rest, without movement.

### Motor performance, upper limb function

The motor performance of the upper limb and its functioning will be evaluated on three occasions (preintervention, postintervention, and 30-day follow-up) using the measures below.

### Shoulder Pain and Disability Index (SPADI)

The SPADI is a questionnaire used to measure dysfunction and disability associated with shoulder pain [50]. The numerical version of the SPADI consists of 13 items, five of which address pain and eight of which address function. Each item is scored on a numerical scale from 0 to 10 points. For the final score, the points are converted into a percentage value (0 to 100%), with higher scores denoting worse shoulder dysfunction. The SPADI has been validated for use in the Brazilian population, with excellent test-retest reliability (ICC = 0.90 to 0.94) [50], and has been used in previous studies involving stroke survivors [51].

### Disabilities of the Arm, Shoulder and Hand (DASH)

The DASH is a questionnaire composed of 30 items developed to measure symptoms and disabilities caused by upper limb disorders in a heterogeneous population, the objective of which is to determine differences between groups of individuals through the comparison of the impact of upper limb disorder (mild, moderate, or severe disability) on physical functions and symptoms. The score ranges from 0 (absence of dysfunction) to 100 (severe dysfunction) [52]. DASH has been used in a previous study involving stroke survivors and demonstrated acceptable reliability (ICC = 0.97 to 0.99) [53].

### Fugl-Meyer Assessment of Motor Recovery after Stroke Scale

Motor function of the upper limbs will be analyzed using the Fugl-Meyer Assessment of Motor Recovery after Stroke Scale, which was designed specifically for the evaluation of patients with hemiparesis stemming from a stroke. The scale is divided into five domains: motor function, sensory function, balance, joint range of motion, and joint pain. The motor function domain includes the measurement of movement, coordination, and reflex activity of the shoulder, elbow, fist, hand, hip, and ankle, totaling 100 points (66 related to the upper half of the body and 34 related to the lower half) [54]. In the proposed study, only the score referring to the function of the upper half will be considered. The results of the scoring system enable the classification of the patient as having mild, moderate, or severe impairment. The Fugl-Meyer Assessment of Motor Recovery after Stroke has excellent reliability, validity, and sensitivity to change [55, 56]. This measure was translated into Brazilian Portuguese based on the original version published in 1975 [54], demonstrating high interobserver and intraobserver reliability for the total scale (ICC = 0.99 and 0.98, respectively) as well as the upper extremity motor function subscale (ICC = 0.99 and 0.98, respectively) [57].

### Shoulder range of motion

A goniometer, which is a device consisting of two plastic rods (one fixed and one movable) and a compass to allow determination of joint angles [58], will be used to measure shoulder angles in the range of external rotation, abduction, and flexion during passive movements performed by the researcher and active movements performed by the volunteer.

### Grip strength

For this evaluation, the volunteer will be seated with the upper limbs supported on the arm rests of the chair and the elbows at 90 degrees. Grip strength will be measured in both hands using the Jamar® dynamometer (Enterprises Inc., Irvington, New York, USA) with the handle in the second position, which results in greater grip strength [59]. The American Society of Hand Therapists also recommends the use of position II as a standard in clinical practice and research during grip strength tests involving the Jamar dynamometer. The reliability of this device is high (ICC > 0.87) [60].

### Quality of life

Quality of life will be measured using the Stroke-Specific Quality-of-Life Scale (SSQOL), which is a standardized, validated scale that specifically addresses the quality of life of stroke survivors [61]. The scale is composed of 49 items distributed among 12 domains. Each item is scored from 1 to 5 points. The total ranges from 49 to 245, with higher scores denoting better quality of life. The SSQOL has a reliability coefficient of 0.92 [61] and has been used in studies with good clinical results [62].

### Determination of potential confounding factors

#### Depressive symptoms

Depressive symptoms will be evaluated and graded with regard to severity using the Beck Depression Inventory (BDI), which is a self-administered questionnaire composed of 21 items. Each item is scored from 0 to 3 points. The total ranges from 0 to 63 points and is interpreted as follows: 0 to 10 indicates the absence of depression; 11 to 18 = mild depression; 19 to 29 = moderate depression; and 30 to 63 = severe depression [63, 64]. The BDI score will be determined on three occasions (preintervention, postintervention, and 30-day follow-up) and will be used as a covariant to determine whether motor recovery is independent of possible mood-related effects [65]. The reliability of the BDI is 0.89 [64] and this measure has been used in studies that have shown good clinical results [62].

#### Sleep disorders

Sleep-related disorders will be analyzed using the Pittsburgh Sleep Quality Index (PSQI). This questionnaire is composed of 24 items, 19 of which are self-administered and subdivided into seven domains: 1) subjective sleep quality; 2) sleep latency; 3) duration of sleep; 4) habitual effectiveness of sleep; 5) sleep disorders; 6) use of sleeping pills; and 7) daytime dysfunctions. Five additional questions are answered by the person who shares the same bedroom as the individual participating in the evaluation. The sum of the seven domains ranges from 0 to 21 points, with higher scores denoting poorer sleep quality. A score greater than 5 indicates major difficulties in at least 2 components or moderate difficulties in more than 3 components. The PSQI will be determined at the preintervention evaluation and 30-day follow-up. The reliability of this measure is 0.82 (general reliability coefficient) [66, 67].

#### Use of medications

The use and amount of medications, such as analgesics, anti-inflammatory agents, antidepressants, and anticonvulsants, will be measured with the aid of a questionnaire designed by the authors of the study, which will contain the complete data of each patient.

#### Intervention

All patients will receive passive manipulations, such as massage, stretching, and passive joint movements, which will be administered by a therapist on the painful upper limb for 20 min. Next, tDCS will be administered over the cerebral cortex and the patient will receive stimulation for 20 min while performing physical activity with the upper limbs (“mini-bike”). The total physiotherapeutic treatment will be 40 min. Active or sham tDCS and physical activity will be performed at a frequency of five sessions per week for 2 weeks, totaling 10 sessions [68].

#### Transcranial direct current stimulation (tDCS)

Stimulation will be performed using the NeuroConn DC-STIMULATOR PLUS and administered over the primary motor cortex (M1) of the damaged hemisphere. Unbalanced bipolar anodal stimulation will be administered with the anode positioned over either C3 (left hemisphere) or C4 (right hemisphere), following the 10/20 electroencephalogram system. The cathode will be positioned in the supraorbital region contralateral to the anode [69]. The cathode will measure 35 cm^2^ (5 × 7 cm) and the anode will measure 25 cm^2^ (5 × 5 cm). Both electrodes will be enveloped in sponge soaked in saline solution. During active tDCS, the intensity of the current will be 2 mA, administered for 20 min.

#### Sham transcranial direct current stimulation

Sham stimulation will be performed with the device in the sham setting. The montage will be the same as that in the active stimulation group, but the device will only be activated for 60 s, with a gradual increase in current during the first 30 s (ramp up) to give the volunteer the sensation of stimulation, followed by a gradual decrease over the subsequent 30 s (ramp down). Sham tDCS will be administered by a therapist who will not participate in the evaluations.

#### Determination of potential side effects

Possible adverse effects stemming from noninvasive brain stimulation will be determined using the TDCS Side Effects Questionnaire (a version translated into Portuguese) after each session and immediately after the intervention protocol [70].

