Considering the relationship between pain and motor performance and the fact that long periods of cortical stimulation can have lasting effects on brain function, such as an increase in the intrinsic plasticity of the motor sensory system and the enhancement of the effectiveness of other therapeutic tools, it is believed that the combination of tDCS and physical therapy may lead to a reduction in pain. This combined therapy is expected to enhance the motor performance of patients with PSSP as well as improve both sleep quality and quality of life. Indeed, stimulation is effective at relieving a number of chronic pain conditions, especially in patients who are resistant to drug therapy [26, 40].

Therefore, the aim of the proposed study is to evaluate the effect of tDCS, when combined with upper limb physical therapy, on pain level and functional improvements in stroke patients with hemiplegic shoulder pain. As a secondary endpoint, we intend to correlate the analgesic effects of tDCS therapy and upper limb physical activity with the effects on motor performance and determine the influence of this therapeutic modality on sleep quality and quality of life.

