## Methods

### Study design

A randomized, placebo-controlled, double-blind, longitudinal, clinical trial is proposed.

The primary outcome of this study will be the intensity of shoulder pain, which will be measured using the visual analog scale (VAS). The VAS will be administered on three occasions): 1) pre-intervention; 2), after 10 interventions; and 3) 30 days after the end of the interventions. The secondary outcomes are motor performance and quality of life.

Participants will be recruited from the physical therapy clinics of the University Nove de Julho, São Paulo, Brazil.

The SPIRIT checklist can be found as Additional file 1. The evolution of the study is shown in Fig. 1.

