### Eligibility criteria

Individuals who meet the following inclusion criteria will be asked to participate in the study: 1) adults (> 18 years of age) with a diagnosis of chronic stroke [41] (there are few studies proving the safe administration of tDCS in the acute and subacute phases of a stroke, hence the choice of chronic stroke) and complaint of shoulder pain after stroke for at least 6 months (the ideal time for research on chronic pain, according to the IASP) [5]; and 2) able to understand commands (Mini-Mental State Examination score > 11) [42].

The exclusion criteria are: 1) contraindication for noninvasive brain stimulation (metal implants near application sites, history of seizures and/or epilepsy, pregnancy, and diagnosis of neoplasm); 2) muscular inelasticity (spasticity) > 3 on the affected upper limb, evaluated by the Modified Ashworth Scale [43]; 3) progressive neurological disease; 4) diagnosis of frozen shoulder; 5) severe sensory deficit (score > 2 on the National Institutes of Health (NIH) Stroke Scale) [44]; 6) diagnosis of acute coronary syndrome or severe heart problems (score > 3 on the New York Heart Association functional classification scale) [45]; 7) severe aphasia (score > 2 (evaluated in patient’s native tongue) indicated by NIH Stroke Scale) [44]; 8) suspicion or confirmation of recent upper limb fracture; 9) diagnosis of cancer and/or in therapy for palliative care; and 7) severe inattention (score > 2 indicated by NIH Stroke Scale) [44]. Concomitant care and interventions prohibited during the trial will be the recent use of botulinum toxin or phenol injection in the affected upper limb (in the previous 3 months) or a medical indication for use during the study period, the use of medications that can affect the evaluations (steroidal anti-inflammatory drugs), and participation in physical or homeopathic therapy during the study.

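### Side effects are scheduled only up to the end of treatment, while benefit is measured to 30 days afterwards

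*Protocol article*

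**What the plan says.** The section Determination of potential side effects names the instrument: "Possible adverse effects stemming from noninvasive brain stimulation will be determined using the TDCS Side Effects Questionnaire". It then gives the timing: "a version translated into Portuguese) after each session and immediately after the intervention protocol". No later reading is named, and no other harm instrument is described in the article.

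Treatment consists of "five sessions per week for 2 weeks, totaling 10 sessions" (Intervention). The section Data collection, management, and analysis places all evaluations at baseline, after the ten sessions, "and 30 days after the end of the treatment sessions (follow-up"). Study design includes that last visit among the three occasions for the primary pain outcome. Later sections place upper limb motor performance and function, the depression inventory and the sleep index at the same visit.

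The Background supports the combined treatment partly on the ground that "long periods of cortical stimulation can have lasting effects on brain function". Eligibility criteria list "history of seizures and/or epilepsy" among the contraindications to stimulation.

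**The concern.** The schedule looks for persisting benefit at a visit where, as described, nobody is scheduled to ask about harm. If the effects of repeated stimulation may outlast the sessions, that possibility covers unwanted effects as well as wanted ones. The Background also says that no tDCS studies were found in shoulder pain after stroke, so by the authors' own account there is little earlier experience in this population to fill the gap.

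What is at stake is the scope of the safety statement. The report would set pain results at 30 days beside side-effect data that stop at the end of treatment. A reader could easily take a sentence on tolerability to cover the whole period of observation, which the scheduled data would not support.

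**Working it through.** The plan gives no figure on this point, so there is none to reproduce. The check compares sections and then does a short calendar calculation.

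**What is scheduled when**

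| Measure | Baseline | Each session | End of treatment | 30 days after |
|---|---|---|---|---|
| VAS pain | yes | no | yes | yes |
| Motor performance and upper limb function | yes | no | yes | yes |
| Depression inventory (BDI) | yes | no | yes | yes |
| Sleep index (PSQI) | yes | no | no | yes |
| Side-effects questionnaire | no | yes | yes | not named |

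Each row follows the measure's own section.

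**Does the general evaluation sentence fill the last cell?** Read literally, it would put every instrument at all three visits. Two things weigh against that reading.

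- The PSQI section gives only baseline and 30 days, so an instrument's own section can depart from the general sentence.
- The side-effects section also gives its own timing, and that timing does not match the three visits. It adds per-session readings, and a baseline reading of stimulation side effects would have no meaning.

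The more natural reading is that the side-effects section governs and day 30 is not included. The text does not settle the matter, so the two sections need reconciling.

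**Length of the two windows**

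Inputs: ten sessions at five per week (Intervention) and a visit 30 days after the last session (Data collection, management, and analysis). The calendar position of the sessions is not given, so I assume weekdays.

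- Monday start: sessions fall on days 1 to 5 and 8 to 12, so treatment spans 12 days. Total observation is 12 + 30 = 42 days. Share with scheduled side-effect collection: 12/42 = 29%. Share without: 30/42 = 71%.
- Midweek start, for example Wednesday: 3 + 5 + 2 sessions across three calendar weeks, so treatment spans 14 days. Total is 14 + 30 = 44 days. Share without: 30/44 = 68%.

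About 68% to 71% of calendar time under observation therefore has no scheduled side-effect collection. This is a share of days, not of expected events. The article gives no basis for saying what fraction of side effects would arise late.

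**Effect of the change on the design.** The questionnaire does not enter the sample size calculation or the primary analysis, so a 30-day reading leaves N, alpha and power as they are.

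**The case against.** The strongest reply is that the section gives the timing of one questionnaire and does not say this is the only route by which an adverse event can be recorded. Spontaneous and serious event reporting is commonly left to the full protocol, which is not shown. That stands, and it limits the point to scheduled collection.

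Three stronger readings are tempting, and the document does not support them.

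- **That a seizure or other event after session 10 would enter no record.** The article is silent on unscheduled reporting. Worsening pain, function, mood or sleep would also show in the 30-day measures, although not labelled as adverse events.
- **That the end-of-protocol reading merely repeats the one after session 10.** The section names two readings. The second may be a whole-course reading at the post-intervention evaluation, whose distance from session 10 is not stated.
- **That the small sample makes the gap worse.** With no events in 13 active patients, the one-sided 95% upper bound is 1 - 0.05^(1/13) = 0.206, or about 21%. That bound comes from the number of patients alone and would be the same with a 30-day reading added.

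It can also be said that the Background speaks of plasticity and enhanced therapy, not of delayed harm, and that safety is not a stated aim. Both are fair. No passage shows that harms of stimulation appear late, and the exclusion for seizure history shows only that the risk is recognised. This argues for a modest grade. It does not remove the point, because the schedule is one the article states, and the visit that could close the gap already takes place.

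**Conclusion.** The point holds as a limit on coverage. The article fixes side-effect collection within the treatment period and describes no scheduled harm collection at the 30-day visit, where benefit is assessed. On a Monday-to-Friday schedule the side-effect data cover about 12 of about 42 days.

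This rests on two assumptions: that sessions fall on weekdays, and that the side-effects section's own timing takes precedence over the general evaluation sentence. If the general sentence is meant to include side effects at day 30, the fault reduces to two sections that disagree. If the full protocol provides for spontaneous reporting, late events have a route to being recorded but are still not asked about on schedule.

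The change is worth making because it is cheap. The primary outcome, sample size and analysis are not affected.

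**What to change.** In Determination of potential side effects:

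1. Keep the reading after each session and the reading at the end of the intervention protocol.
2. Add a reading at the existing 30-day visit, using either the same questionnaire or an open adverse-event question, that covers the whole interval since session 10.
3. State how this timing relates to the general sentence in Data collection, management, and analysis, so that the two sections agree.
4. Report on-treatment and post-treatment events separately, by arm.

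Trial status says that recruitment was under way at submission and gives November 2018 as the expected completion, which is before the article's publication in March 2019. A prospective change may therefore reach few patients or none. For patients already past day 30, limit any tolerability statement to the treatment period.

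Cost: one sentence of amendment and one short questionnaire per patient, taking the scheduled readings from 11 (ten sessions plus one) to 12, with no extra visit. The drawback is that recall over 30 days is less reliable than same-day reporting, which is another reason to present the two periods separately.

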#### Physical therapy

Physical activity will consist of active movements of the upper limbs using a “mini-bike” (Acte Sports, model E5). For this, the patient will be positioned in a chair with a 90° backrest and feet resting on the floor. The mini-bike will be positioned on a table, which will allow free arm movements. The patient will perform active movement or active-assisted movements (if the patient cannot hold onto the handle, the therapist will assist by securing the patient’s hand on the handle) [71]. This activity will be performed for 20 min concomitantly with tDCS.

#### Data analysis

Descriptive data and characteristics of the patients (gender, age, initial score on the VAS, ischemic or hemorrhagic stroke, right/left hemisphere lesion, time with pain, injury time, Fugl-Meyer upper limb score, BDI, use of controlled medications, and associated comorbidities) will be represented by mean and standard deviation or median and interquartile range. The normality of the data from the VAS, DASH, Fugl-Meyer, SSQOL, range of motion passive shoulder, and hand grip strength will be analyzed by the Shapiro-Wilk test.

If the normality hypothesis is accepted, the analysis of variance (ANOVA) followed by the Bonferroni test will be used, when necessary, to perform the comparison analysis between groups. If the normality hypothesis is rejected, the Kruskal-Wallis test will be used. The Mann-Whitney test will be used to compare the results of the study treatment periods (pre- and post-treatment and 30-day follow-up). Pearson or Spearman correlation coefficients will be calculated to determine the strength of correlations between pain and secondary outcomes (SPADI, Fugl-Meyer, SSQOL, passive shoulder range of motion and grip strength). A value of *p* < 0.05 will be considered indicative of statistical significance. All analyses will be processed using the SPSS program (IBM SPSS Statistics for Windows, Version 22.0, released in 2013, IBM Corp., Armonk, NY, USA).

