### Sample size

For the calculation of the sample size, the primary endpoint of the study (shoulder pain intensity at rest measured by VAS) was considered to be directly related to the intervention and has been widely used for this purpose. The calculation was performed considering a level of significance (alpha) of 0.05 and an 80% study power, considering a clinically important difference of ≥ 3 points on the VAS [46]. Based on the results of a pilot study involving 10 individuals with PSSP (five for the active group and five for the sham), the difference between the means was 3.0 in the group submitted to physical therapy, and active tDCS and 1.56 in the submitted group to physical therapy and sham ETCC, with a combined standard deviation of 1.38, the required sample size was 22 subjects (11 per group). Taking into account the possibility of dropouts, the sample was increased by 20% to ensure a sample size that enables us to demonstrate the effect of the intervention, leading to 13 individuals in each group (total of 26 participants). This calculation was performed using the G*Power software.

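### If the planned ANOVA is the classical repeated-measures form, patients who miss the 30-day visit lose their recorded post-intervention VAS; a baseline-adjusted mixed model would keep it

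*Protocol article*

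**What the plan says.** All places are in the Methods of the protocol article.

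- **Pain intensity:** the VAS is taken "on three occasions: preintervention, postintervention, and 30-day follow-up". Pain at rest is the value that counts.
- **Randomization:** there are two groups, active and sham tDCS, each with the same physical therapy.
- **Data analysis:** if normality is accepted, "the analysis of variance (ANOVA) followed by the Bonferroni test will be used, when necessary, to perform the comparison analysis between groups". If it is rejected, Kruskal-Wallis is used. A separate sentence names Mann-Whitney for comparing the treatment periods. On software: "All analyses will be processed using the SPSS program".
- **Sample size:** 11 patients per group are required. Then: "Taking into account the possibility of dropouts, the sample was increased by 20" per cent, giving 13 per group and 26 in total. When dropouts are expected is not stated.

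The article does not mention repeated measures, a time factor, listwise deletion or a particular SPSS procedure.

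**The concern.** The article names a method for the primary comparison, and the most coherent reading of that method limits which patients count. With two arms, a Bonferroni follow-up between groups has nothing to correct. It gains a purpose once the three visits enter the same ANOVA, and Study design does call the trial longitudinal.

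A classical repeated-measures ANOVA works on one complete row per patient. Someone who finishes the ten sessions, gives a post-intervention VAS and then misses the 30-day visit is removed from the post-intervention comparison too. This has two consequences. Readings already recorded are discarded in a trial of 26 patients. And membership of the post-intervention comparison depends on later attendance, which may be related to pain or to arm.

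**Working it through.** **Inputs (Sample size section).** "The calculation was performed considering a level of significance (alpha) of 0.05 and an 80% study power"; "the difference between the means was 3.0 in the group submitted to physical therapy, and active tDCS and 1.56 in the submitted group"; "with a combined standard deviation of 1.38". The difference is 3.0 − 1.56 = 1.44, and d = 1.44 / 1.38 = 1.043. Sidedness is not stated; two-sided is assumed below.

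**Step 1: which test reproduces the plan's figure?** The stated result is "the required sample size was 22 subjects (11 per group").

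- Two-sided two-sample t-test: 16 per group are needed for 80% power (15 by the normal approximation). At 11 per group, power is 64%.
- One-sided: 12 per group (normal approximation) or 13 (t).
- Repeated-measures ANOVA, between-groups F test, three visits: f = d/2 = 0.522 and noncentrality = N × f² × 3 / (1 + 2ρ). With an assumed between-visit correlation ρ = 0.5 and N = 22, this is 22 × 0.272 × 3 / 2 = 8.98, and power is 0.81. The required N is 22 at ρ = 0.5, 18 at ρ = 0.3 and 26 at ρ = 0.7.

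So 22 fits a three-visit repeated-measures calculation at ρ = 0.5. The document does not give ρ, so this supports the reading without proving it.

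**Step 2: largest possible loss at the post-intervention visit.** Assume that all 26 attend that visit, 20% then miss day 30, and incomplete patients are deleted. This leaves 26 × 0.8 = 20.8, about 21 patients. SE = 1.38 × √(1/n₁ + 1/n₂); power is from the two-sided noncentral t.

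| Patients analysed | SE | Power |
|---|---|---|
| 13 + 13 (all post readings kept) | 0.541 | 72.3% |
| 11 + 11 (plan's evaluable target) | 0.588 | 64.4% |
| 11 + 10 | 0.603 | 62.0% |
| 10 + 10 | 0.617 | 59.8% |

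Simulated deletion of 20% at random gave an SE of about 0.61, an increase of about 13%. The upper bound is therefore 72% falling to about 60–62%.

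**Step 3: other dropout timings.** If every dropout leaves before the post-intervention visit, there is no post reading to discard and the loss is zero. Mixed timings lie in between.

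**Step 4: against the plan's own target.** From 64.4% at 11 + 11 to 62.0% or 59.8% is 2–5 points. On the repeated-measures F test at ρ = 0.5, power is 0.81 at N = 22, 0.79 at 21 and 0.77 at 20.

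**Step 5: does the replacement need baseline?** Assume a VAS SD of 1.8 and a between-visit correlation of 0.7. The change SD is then 1.8 × √(2 × 0.3) = 1.39, close to the plan's 1.38. With 13 per arm:

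- Post values without baseline: SE = 1.8 × √(2/13) = 0.71, power 50%.
- Baseline as covariate: residual SD = 1.8 × √(1 − 0.49) = 1.29, SE = 0.50, power about 78%.

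A mixed model without baseline would do worse than the deletion it is meant to cure. With baseline it does better.

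**The case against.** The strongest objection is that the procedure is inferred. The ANOVA sentence speaks of comparing groups, its non-normal fallback is an independent-samples test, and the periods are compared in another sentence. All of that fits a separate ANOVA at each visit, under which a patient who misses day 30 keeps the post-intervention reading. Listwise deletion belongs to one SPSS procedure, not to ANOVA or SPSS in general. This stands, and it makes the point conditional. It does not remove it: a per-visit ANOVA leaves Bonferroni between two arms without a role, and the Mann-Whitney test named for the periods does not suit repeated readings on the same patients, so those test names are weak evidence of a deliberate per-visit design.

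A second objection is that an article may leave missing-data handling and analysis sets to the full protocol or SAP. That is right, and silence on them is not the complaint here. The point concerns the method that is named.

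A reader might also infer more than the document supports:

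- **That the plan drops every patient with a missing visit.** The text does not say this.
- **That the whole 20% lose observed post readings.** Dropout timing is not given, and patients who leave during treatment have no such reading to lose.
- **That power falls 10–12 points below plan.** That compares with 13 evaluable per arm; the plan needs 11 and added patients to absorb losses.
- **That the result would be biased by a known amount.** Assumed pain-related dropout models moved the complete-case difference from 1.44 to 1.37 or to 1.57, in opposite directions. Another model with the same mechanism in both arms gave essentially no bias. Dependence on later attendance is a real weakness, but its size cannot be stated.

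**Conclusion.** The point holds conditionally. The Data analysis section most naturally describes a group-by-visit repeated-measures ANOVA. If it is run classically, it excludes recorded post-intervention VAS values of patients who miss day 30.

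The cost at the post-intervention visit ranges from nothing to an SE increase from 0.54 to about 0.61, with power going from 72% to about 60–62%. The upper end requires that all 20% are lost after that visit; all of these figures use the plan's difference and SD and a two-sided test. Against 11 per arm the shortfall is 2–5 points. Most of the gap to 80% on a two-sided t-test is already there at 11 per arm (64%) and is not caused by this issue.

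A change is still worth making. Adding patients to cover losses is no reason to discard readings already in hand, and the recommended model loses nothing if a per-visit analysis was intended.

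**What to change.** In Data analysis, replace the ANOVA for the VAS and the other continuous outcomes by a linear mixed model for repeated measures (SPSS MIXED):

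- all randomised patients in their allocated arm, using every available post-intervention and 30-day reading;
- the baseline value of the outcome as a covariate;
- arm, visit and arm-by-visit as fixed effects;
- a pre-specified within-patient covariance and Satterthwaite degrees of freedom;
- the arm difference with 95% CI at each visit.

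Keep the complete-case ANOVA as a sensitivity analysis, and state that it is repeated-measures if that is what was meant.

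The cost is wording only: no extra patients, visits or software. The covariance structure must be fixed in advance. The model assumes that missingness is explained by the observed data, which is weaker than what the complete-case ANOVA needs. A patient with no reading after baseline still contributes no outcome information.
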